The ankle-arm index (AAI) is the result of the quotient obtained by dividing systolic arterial pressure (SAP) at the level of the posterior pedial or tibial artery between the brachial SAP by Doppler [6]. Low values of AAI determination (<0.9) allow the diagnosis of peripheral arterial disease (PAD) in asymptomatic patients [7]. An AAI of < 0.9 has a sensitivity of 95% and a specificity of 99% for angiographically demonstrated PAD [8]. Determination of the AAI also allows the quantification of the severity of PAD: mild (AAI = 0.7 – 0.9), moderate (AAI = 0.5 – 0.69) and severe stenosis (AAI = <0.5).

In some studies a low AAI has shown to be a good marker of vascular events [8]. In the Atherosclerosis Risk in Communities (ARIC) Study [9,10], the AAI was inversely associated with coronary disease, ictus and atherosclerosis at the level of the carotid and popliteal arteries. The Edinburgh Artery Study [11] reported a relative risk of ictus of 1.98 (CI 95%; 1.05 – 3.77) in patients with an AAI < 0.9. In a Swedish cohort of males over the age of 68 years [12] followed over 10 years, the relative risk of ischaemic ictus for an AAI = 0.9 was 2.0 (95% CI; 1.1 – 3.7). These results, however, do not agree in all studies. In the Cardiovascular Health Study [7], an assocation was found between a low AAI and the risk of vascular events in general, but no relationship was observed between an AAI < 0.9 and the risk of ictus. In addition, in the Pittsburgh study the risk of cardiovasscular events significantly increased only above an AAI < 0.7 [13].

Another aspect requiring clarification is the prognostic value of AAI in a medium with a low prevalence of cardiovascular diseases such as in Spain and other Mediterranean countries [14].

Moreover, the PAD is a significant predictor of cardiovascular mortality [15-17]. Mortality is also greater in patients with asymptomatic PAD compared to patients without arterial disease [16,18,19]. Some studies [7] have suggested that PAD in females represents a greater cardiovascular morbidity while in males this disease represents a higher mortality rate.

The prevalence of PAD ranges between 1.8% and 25% according to the population, the medium studied and the cut-off value of the AAI [11,20-25]. Likewise, the prevalence is higher in determined populational subgroups such as diabetics [20] and smokers [23]. No populational based studies are available in Spain, with the studies found being carried out in selected populations [26-34].

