The present study will have two phases. The main objective of the first phase (cross-over study) is to determine the prevalence of PAD in the general population, in both its silent and symptomatic forms. The secondary objective is to study the association of PAD, especially in the silent forms, with other prevalent cardiovascular events and cardiovascular risk factors. The main objective of the second phase (cohort study) is to determine the incidence of cardiovascular events in patients with PAD and quantify the risk of having these events. The secondary objective in this phase is to study the predictive value of AAI with respect to the risk of having cardiovascular events in relation to the equations of cardiovascular risk (Framingham-Wilson, Framingham calibrated by REGICOR and SCORE).

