## Methods/Design

This is a two-phase study. The first phase is a transversal, multicentre, descriptive study the aim of which is to determine the prevalence of symptomatic and asymptomatic PAD in a general population attended in primary care. The secondary aim is to study the association of PAD, especially in the silient forms, with other previous or prevalent cardiovascular events and cardiovascular risk factors. The second phase is a cohort study, the main objectives of which are to determine the incidence of cardiovascular events in patients with and without PAD and to quantify the risk of having these events. The secondary objective is to study the predictive value of AAI with respect to the risk of having cardiovascular events in relation to the equations of cardiovascular risk (Framingham, Framinham calibrated by REGICOR and SCORE). An initial 5-year follow up will be carried out in the cohorts generated in phase I: subjects without PAD and subjects with PAD and the cardiovascular morbimortality will be analysed. This study has been approved by the local Ethics Committee (Jordi Gol i Gurina Foundation of Investigation in Primary Care). Informed written consent will be obtained from all the participants. Likewise, the recommendations of the World Medical Assocation Declaration of Helsinki will be followed [35].

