#### Follow up (cohort study)

After determination of the AAI the subject will enter in one of the cohorts (AAI>= 0.9: cohort without peripheral arterial disease; AAI < 0.9 cohort with peripheral arterial disease).

The successive controls will be undertaken every 6 months after the last visit, by telephone interview. The appearance of any of the events will be registered in the data collection protocol: transitory ischaemic accident, ictus, angina, myocardial infarction, symptomatic abdominal aneurysm and mortality attributable to vascular causes.

The main variable of response will be the appearance of cardiovascular events as a combined compound variable [27] made up of the following diseases:

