#### Data analysis

This will be performed with the Stata 9 statistical package after the introduction of the data in a database (Acces).

Quantitative variables will be compared with the Student's t test and analysis of variance (ANOVA) will be performed, using the corresponding non parametric tests when necessary. Qualitative variables comparisons will be determined using the Chi squared test.

An analysis of survival of each vascular event will be performed according to the presence/absence of PAD with the Kaplan-Meier curves. Cox multivariate regression models will be used to compare the probability of having a cardiovascular event in the follow up cohorts, adjusting for the necessary covariables. The relative risk (hazards ratio) will be analysed with a confidence interval of 95%.

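### Kaplan-Meier curves for each vascular event censor competing deaths, so any event incidence read from them as 1-KM is overstated, by an amount the protocol does not allow one to fix

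*Protocol article*

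**What the plan says.** The Methods/Design section sets out the aims of phase 2 in these words: "the main objectives of which are to determine the incidence of cardiovascular events in patients with and without PAD". Measuring how large that risk is forms the other main aim. The Background gives the same aim for the PAD cohort: "determine the incidence of cardiovascular events in patients with PAD and quantify the risk of having these events". Follow-up is fixed as follows: "An initial 5-year follow up will be carried out in the cohorts generated in phase I".

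The endpoint is defined under Follow up (cohort study): "The main variable of response will be the appearance of cardiovascular events as a combined compound variable". The events registered there end with "symptomatic abdominal aneurysm and mortality attributable to vascular causes", and the Mortality subsection lists vascular causes of death only. Non-vascular death is therefore not an event.

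The Data analysis section gives two time-to-event methods. The first is descriptive: "An analysis of survival of each vascular event will be performed according to the presence/absence of PAD with the Kaplan-Meier curves". The second is comparative: "Cox multivariate regression models will be used to compare the probability of having a cardiovascular event in the follow up cohorts", reported as a hazard ratio with a 95% confidence interval. Competing risks, cumulative incidence functions and the handling of other deaths are not mentioned.

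On mortality by PAD status, the Background says: "Mortality is also greater in patients with asymptomatic PAD compared to patients without arterial disease".

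**The concern.** A Kaplan-Meier curve for one type of event has to treat a person who dies of something else as censored, that is, as someone who could still have the event later. 1-KM then describes a setting in which nobody dies of other causes. It is not the proportion of the cohort that has the event.

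Which deaths compete depends on the curve:

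- For a single event such as infarction, every death not due to that event competes, including vascular deaths of another type.
- For the composite, only non-vascular deaths compete.

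Such deaths will occur. The Abstract recruits people over 50, the Discussion provides for patients over 74, and follow-up is 5 years. By the Background's national figure, 34% of deaths are cardiovascular, so 100 − 34 = 66% are not.

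What is at stake is the absolute incidence by PAD status, which is a main objective and would inform any screening use. If competing deaths are more frequent with PAD, the relative overstatement is also larger there.

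**Working it through.** **Inputs from the protocol article**

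- Incidence 5.2% and minimum relative risk 2 (Sample size), which give 5.2% without PAD and 2 × 5.2 = 10.4% with PAD.
- Follow-up 5 years (Methods/Design).

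**Assumptions**

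- The 5.2% is a 5-year risk in the group without PAD. The article states no time span and attributes the figure to the general population.
- Hazards are constant, and 5.2% and 10.4% are the values that 1-KM would show.
- Five-year competing mortality is 2–10% without PAD and 4–30% with PAD. The document gives no such rate.

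**The plan's own figure.** The article gives no competing-mortality figure to reproduce. Its sample size (301 with PAD, 2709 without) can be approached from the same risks. Take a ratio of 1:9, two-sided alpha 0.05, power 0.80 and an unweighted mean proportion of 7.8%:

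n = [1.96·√((1 + 1/9)·0.078·0.922) + 0.84·√(0.104·0.896 + 0.052·0.948/9)]² / 0.052² = 247.7

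A continuity correction gives 268.6, and dividing by 0.9 for loss gives 299. Reading 5.2% as the whole-population incidence, without the continuity correction, gives 306. Both are within 3% of 301, so the sample size does not settle which reading was meant. The present point does not rest on it.

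**Formulas.** Let e be the 1-KM event risk and c the competing mortality over 5 years.

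- Event hazard: λ = −ln(1 − e)/5
- Competing hazard: μ = −ln(1 − c)/5
- 1-KM = 1 − exp(−5λ) = e
- Cumulative incidence = λ/(λ + μ) × [1 − exp(−5(λ + μ))]

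**Example, PAD with c = 20%.** 5λ = 0.1098 and 5μ = 0.2231. The ratio λ/(λ + μ) is 0.3298, and 1 − 0.896 × 0.80 = 0.2832. Cumulative incidence = 0.3298 × 0.2832 = 9.34%, against 10.40% by 1-KM. Relative overstatement = 10.40/9.34 − 1 = 11.3%.

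**Results**

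| Competing mortality, no PAD / PAD (assumed) | No PAD: 1-KM vs cumulative incidence | PAD: 1-KM vs cumulative incidence |
|---|---|---|
| 2% / 4% | 5.20 vs 5.15% (1.0% relative) | 10.40 vs 10.19% (2.0%) |
| 5% / 10% | 5.20 vs 5.07% (2.6%) | 10.40 vs 9.88% (5.3%) |
| 10% / 20% | 5.20 vs 4.94% (5.3%) | 10.40 vs 9.34% (11.3%) |
| 10% / 30% | 5.20 vs 4.94% (5.3%) | 10.40 vs 8.78% (18.5%) |

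**Two checks**

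- The relative size hardly depends on the event risk. With a 4% event risk in PAD it is 2.0%, 5.3% and 11.5% at competing mortality of 4%, 10% and 20%. This covers rarer single events and weakens the dependence on how the 5.2% is read.
- With equal competing mortality of 10% in both cohorts, the relative overstatement is 5.3% in each. A larger relative bias in PAD therefore needs higher competing mortality in PAD.

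**The case against.** The strongest reply is that the article never says incidence will be read from 1-KM. Kaplan-Meier is assigned to survival curves by PAD status, the incidence objective names no estimator, and rates per person-time, for which ending follow-up at death is correct, would be compatible with the text. Rules for censoring are also commonly left to a fuller document. This stands in part: nobody can say from the article that the reported incidence will be biased. But the method is stated, not omitted. It is the only time-to-event description of event occurrence that the article names, and a Kaplan-Meier curve for one event type censors other deaths whether or not the text says so.

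Three stronger readings are tempting and should not be drawn:

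- **The effect estimate is biased.** A reader might infer this from the Cox sentence, which speaks of comparing probabilities. The cause-specific hazard ratio remains a valid comparison of rates, and the sample size does not change. Only the description as a comparison of probabilities is wrong.
- **The composite is certainly more overstated, in relative terms, in PAD.** The Background sentence on mortality does not separate out non-vascular death and follows a statement about cardiovascular mortality. Excess vascular death is an event in the composite, not a competing risk. For single-event curves the inference is better founded, because other vascular deaths compete there.
- **The risk difference between cohorts is exaggerated by a known amount.** With 20% competing mortality in PAD and 5% without, 1-KM shows 10.40 − 5.20 = 5.2 points where cumulative incidence shows 9.34 − 5.07 = 4.3. But that mortality contrast is assumed, and the article does not plan to report a risk difference.

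The size may also be modest. With 301 PAD subjects, the standard error of 10.4% is √(0.104 × 0.896/301) = 1.8 points, against an overstatement of 0.21 points at 4% competing mortality and 0.52 at 10%.

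**Conclusion.** The point holds in a limited form. The named curves overstate event probability whenever competing deaths occur, most clearly for single events, and they do not fit an objective stated as an incidence. The direction follows from the method. The size does not follow from the document: under the assumptions above it is about 2% to 11% relative in the PAD cohort for competing mortality of 4% to 20%, and 18.5% at 30%. At the low end it is negligible beside sampling error. A larger overstatement in PAD is probable for single-event curves and only an inference for the composite. The change is worth making because the better method is standard and cheap, not because the study's main comparison is in danger.

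**What to change.** In the Data analysis section:

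- Present cumulative incidence functions (Aalen-Johansen) by PAD status in place of Kaplan-Meier curves. Non-vascular death is the competing event for the composite; any other death, vascular or not, is the competing event for each single event.
- Record the date and cause of every death, not only vascular deaths, from the sources already listed in the Mortality subsection.
- Keep the Cox model and its 95% confidence interval. Call the result a cause-specific hazard ratio and drop the description of it as a comparison of probabilities.

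The cost is a little more analysis work, confirmation that all deaths are captured with cause, and slightly lower reported incidences. Sample size and follow-up do not change.

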## Discussion

The aim of the PERART study is to evaluate the real prevalence of peripherial arterial disease in the general population which remains to be determined in Spain and is poorly known in countries with a low cardiovascular risk. These data will be the main contribution of this study since, to date only data of series of patients and very selected populations have been established.

With the present study we hope to demonstrate that the silent forms of peripheral arterial disease may be a marker of cardiovascular risk with a better adjustment than the methods based on risk tables since these are indicative of real damage in the cardiovascular system still in presymptomatic stages.

It is therefore important to keep in mind that the AAI may have a predictive value which is higher than the traditional methods of calculating cardiovascular risk since these methods are based on probabilistic mathematical equations while the AAI detects early stages of atherosclerotic disease. On being a systemic disease, the detection of peripheral involvement is probably indicative of asymptomatic involvement of other vascular territories, and thus, the determination of AAI may have diagnostic and prognostic significance in the detection of asymptomatic cerebrovascular disease. Another interesting aspect is the follow up of the patients with a high AAI, which may also indicate a certain risk of having cardiovascular events if associated with arterial calcification [32].

If the results confirm our hypothesis we will have an easy, accessible, inexpensive test, which is reproducible in Primary Care and which will allow a better selection of patients in whom an approach of greater therapeutic intensity may be applied to thereby avoid or slow major cardiovascular complications and events. We may then have a test to allow screening for selecting patients prior to performing more complex tests or to decide whether to intensify the interventions in lifestyle or with drugs (statins, acetylsalicillic acid, etc.)

On the other hand, the populational, multicentric, prospective design of the study, which collects most of the cardiovascular risk factors will allow our cohort to be used to verify the validity of the existing cardiovascular risk factors or those of other similar future projects within the age range of this study.

